|                                                                                                                                                                                                                                    |                                                                                                                                                            |                                                                     |                                                                                                    |
|------------------------------------------------------------------------------------------------------------------------------------------------------------------------------------------------------------------------------------|------------------------------------------------------------------------------------------------------------------------------------------------------------|---------------------------------------------------------------------|----------------------------------------------------------------------------------------------------|
|                                                                                                                                                                                                                                    | the intervention and after the end                                                                                                                         |                                                                     |                                                                                                    |
| Evaluate the effect of the intervention on the knowledge, attitudes and practices (including history of vaccine hesitancy) of parents with regard to HPV infection and HPV vaccine (Secondary Obj 1)                               | Before-after change in percentages or medians of scores obtained on the Likert scales of the questionnaire addressed to parents                            | KABP-6C questionnaire (see appendix 2 )             | Before the intervention
+ 2 months after the end of the intervention                            |

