## **11.2. Sample size calculation**

The sample size will depend on the number of participating middle schools, which is not known at this stage. This is why at this stage, we will consider the situation of a single middle school per municipality. The calculation below is therefore conservative.

According to government statistics, the number of students per middle school is on average 466. Assuming one middle school per cluster, the average size of the cluster would therefore be 466 adolescents aged 11 to 14. Twenty percent of middle schools having fewer than 300 students and 13% having more than 700, we retain a coefficient of variation of 0.5 in the size of the clusters.

The intra-class correlation coefficient is set at 0.05.

The current prevalence of initiation of vaccination from 11 to 14 years old is 16.1% among girls and 0% among boys due to the date of application of the HAS recommendation on the vaccination of boys. Girls representing 48.85% of the population in this age group, the prevalence among 11-14 year olds is 7.86%. The objective of the intervention is to increase this prevalence by at least 10% (based on data published in the literature). Considering two groups, we would need 15 clusters per group to reach a power of 90% and considering an alpha risk of 5%.

This research will include 6 groups, and the analysis will be carried out using a modeling approach in which several parameters will be tested: effects of interventions, and potential interactions between interventions. It is not planned to make multiple 2 to 2 comparisons. Therefore the alpha risk has not been corrected.

In the end, knowing that 6 groups will be formed, we plan to include a total of 90 municipalities (15 per group). This corresponds to an expected sample of 41,940 adolescents aged 11 to 14, under the assumption of a single middle school per municipality.

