### **11.3.1. Analysis of the primary outcome**

The prevalence of vaccination (at least 1 dose received and complete vaccination) among adolescents aged 11-14 is calculated (from SNDS data, supplemented where appropriate with data from vaccination centers, family planning centers and vaccines delivered in middle school) at the different measurement times (before intervention, 2 months, 6 months and 12 months after intervention) and in each of the six study groups. A calculation of this prevalence according to the sex and deprivation level of the municipality of residence of the adolescents is also planned.

Concerning the analysis of the primary outcome (vaccination coverage rate), an analysis at the cluster level will be carried out, that is to say that the unit of analysis will be the municipality and not the adolescent who is nested in his or her municipality. The data will be collected at the municipality level. Each municipality (= cluster) will be weighted by its size. A modeling approach will be used, carrying out a global analysis of the 90 randomization units. The model will be a linear model in which we will consider 3 fixed effects (one per component) and potential interactions between component. The baseline VC will be considered as an adjustment variable.

The evolution of the VC over time (M2, M6, M12) will also be modeled by considering a longitudinal model, and adjusting for the baseline VC rate.

Subgroup analyzes will be carried out according to sex, deprivation level (FDep) and considering a modeling approach with interaction terms.

Depending on the quality of the data reported by vaccination centers and family planning centers, sensitivity analyzes will be carried out to take into account only SNDS data and the number of vaccines delivered in middle school.

The analyzes are carried out using SAS software version 9.4 or later (SAS Institute Inc.) or R, and considering two-sided statistical tests and a level of significance of 5%.

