### **11.3.2. Analysis of secondary outcomes**

#### **(i) Analysis of secondary objective 1**

For the analysis of this objective, people with a positive change in intention/vaccination will be identified (change from “no” for both at T0 to “yes” for one of the two at T1).

The variables corresponding to the KABP-6C items will be created in particular by calculating knowledge scores and Likert scale medians.

For an analysis of T0, the percentages and medians of the items will be presented by intervention group, namely:

- a. By EMM groups 0 and 1, among participants without vaccination campaign, without taking into account the GP intervention
- b. By school interventions (campaign + EMM vs. without campaign or EMM), without taking into account the GP intervention
- c. By GP groups 0 and 1, among participants with EMM, without taking into account the vaccination campaign intervention

For an analysis of the main effects, the percentages of people with change and the medians of the differences will be presented by group (see a., b., and c.).

The differences will be tested first by suitable non-parametric tests (Fisher's and Wilcoxon, ranksum).

Multilevel models with a binary or continuous (linear) dependent variable will then be constructed in order to estimate the effect of interventions alone or in interaction, while taking into account intraclass correlation effects (cluster randomization). The interactions to be studied as a priority are:

- between the GP intervention and the school intervention (EMM+campaign),

- between the vaccination campaign intervention and the GP intervention (only possible in combination with EMM)
- between the EMM intervention and the GP intervention (only possible in the absence of a vaccination campaign)

For an analysis not taking into account individual evolution between T0 and T1, the effect of each intervention (alone or in interaction) will be estimated from a difference-in-difference model, i.e. including an interaction between the intervention group (among the 6 defined, with the control group as reference) and the temporal indicator “after” (vs. before) intervention.

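### KABP-6C effects (secondary objective 1) are framed as before-after changes with no stated adjustment for T0, which gives up precision the collected baseline could supply

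*Protocol*

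**What the plan says.** The outcome table in protocol section 3.2.1 defines the KABP-6C outcomes as changes between before and after the intervention. For parents' scores, for example, the result is "Before-after change in percentages or medians of scores obtained on the Likert scales of the questionnaire addressed to parents".

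Section 11.3.2 (i) then plans four things:
- A binary outcome marks people who answered no to both intention and vaccination at T0 and yes to at least one at T1.
- For the main effects, "the percentages of people with change and the medians of the differences will be presented by group", in three groupings (a, b and c), tested first with Fisher and Wilcoxon tests.
- Multilevel models with a binary or continuous dependent variable follow. The text does not say whether that variable is the change or the T1 value, and it names no covariates.
- For an analysis that disregards individual evolution between T0 and T1, "the effect of each intervention (alone or in interaction) will be estimated from a difference-in-difference model", with an interaction between group and the after-period indicator.

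Section 7.4 provides an inclusion number that links T0 and T1. For the primary outcome, section 11.3.1 takes baseline coverage as an adjustment variable. Section 11.3.2 (i) has no matching sentence for the KABP-6C effects.

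**The concern.** Municipalities are randomised, so their expected T0 values are equal across groups. Subtracting T0, or fitting a free group effect at T0, fixes the slope on T0 at 1 and carries the full T0 sampling noise into the effect estimate. Using T0 as a covariate lets the data set the slope. In large samples this is never less precise, and for every correlation below 1 it is more precise. Below a correlation of 0.5, subtraction does worse than leaving T0 out.

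At stake are wider intervals for effects on intention, knowledge and attitudes, with 15 municipalities in each randomised group and a T0 survey whose cost is already carried. An analysis plan that follows the outcome definitions literally would model changes.

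**Working it through.** **The plan's own figure.** Section 11.2 states that "we would need 15 clusters per group to reach a power of 90"%. Its inputs are 7.86% against 17.86% (the +10 read as percentage points), two-sided 5%, mean cluster size 466, coefficient of variation 0.5 and ICC 0.05.
- Individually randomised size: 234 per group.
- Design effect: 1 + ((1 + 0.5²) × 466 - 1) × 0.05 = 30.075.
- Clusters: 234 × 30.075 / 466 = 15.1 per group. Power with 15 is 89.9%.

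The figure reproduces. It concerns vaccination coverage only; the protocol has no sample size, ICC, SD or T0-T1 correlation for KABP-6C.

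**Variance of the two contrasts.** Let rho be the T0-T1 correlation of the unit analysed, with equal variances at both times. Relative to a comparison of T1 alone:
- change or difference-in-difference: 2(1 - rho)
- T1 with T0 as covariate: 1 - rho²
- ratio: (1 - rho²) / [2(1 - rho)] = (1 + rho)/2

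| rho (assumed) | change / DiD | T0 as covariate | ratio | variance saved |
|---|---|---|---|---|
| 0.3 | 1.40 | 0.91 | 0.65 | 35% |
| 0.5 | 1.00 | 0.75 | 0.75 | 25% |
| 0.7 | 0.60 | 0.51 | 0.85 | 15% |
| 0.9 | 0.20 | 0.19 | 0.95 | 5% |

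**Which rho is plausible for cluster means.** With m respondents per municipality, cluster autocorrelation pi and individual autocorrelation tau (0 if unlinked), rho = (m × ICC × pi + (1 - ICC) × tau) / (m × ICC + 1 - ICC). I assumed ICC 0.05, m from 30 to 200, pi from 0.5 to 0.95 and tau from 0 to 0.7. The ratio then runs from 0.65 to 0.96, a standard error about 19% to 2% smaller.

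**Finite-sample check.** A simulation of 15 v 15 clusters (4,000 runs, 100 linked respondents each, pi 0.8, tau 0.5) gave a ratio of 0.91, against 0.88 by formula. Estimating the slope with 30 clusters costs a little of the gain but does not remove it.

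**Illustrative power.** Assumptions: 233 respondents per municipality (466 / 2), 50% in control, a 10-point difference, ICC 0.05 borrowed from coverage, two-sided 5%. The variance of a cluster percentage is 0.25 × (0.05 + 0.95/233) = 0.01352. With K clusters per side:
- SE(DiD) = √(2 × 0.01352/K × 2(1 - rho))
- SE(adjusted) = √(2 × 0.01352/K × (1 - rho²))
- Power from the noncentral t, with 2K - 2 and 2K - 3 degrees of freedom.

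| rho | 15 v 15: DiD v adjusted | 30 v 30: DiD v adjusted |
|---|---|---|
| 0.3 | 49% v 66% | 79% v 93% |
| 0.5 | 62% v 75% | 91% v 97% |
| 0.7 | 84% v 89% | 98.8% v 99.6% |

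The 15 v 15 column is one group against control, the reference in the difference-in-difference model. The 30 v 30 column matches groupings a to c, each of which pools two groups per side.

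**The case against.** **Difference-in-difference is not the whole plan.** It applies only to the analysis without the individual link. A reader might infer that all KABP-6C effects are estimated that way; the opening condition of the sentence rules this out.

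**The linked models are left open.** A reader might infer that T0 adjustment is excluded. It is not: dependent variable and covariates are unstated, and the statistical analysis plan may settle them. A linear model of change with T0 as covariate gives the same intervention estimate as T1 with T0 as covariate. What stands is narrower: the stated outcomes are changes, and no adjustment is stated.

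**T0 is not used only by subtraction.** The binary positive-change outcome is a transition, to which 2(1 - rho) does not apply, and T0 values also serve for stratified analyses.

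**Difference-in-difference buys robustness.** This is the strongest argument. T0 respondents are volunteers surveyed in December 2020, after allocation. Section 7.2 has families in the 60 EMM municipalities told of their component at the end of 2020. If a stable difference d in who responds appears at both times, difference-in-difference removes it, whereas adjustment with a slope near rho leaves about (1 - rho) × d. This is a good reason to keep difference-in-difference as a check and not to impose equal group means at T0. It does not justify leaving T0 out as a covariate.

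**The power figures are soft.** The phrase "considering two-sided statistical tests and a level of significance of 5"% belongs to the primary analysis. For KABP-6C the protocol sets no significance threshold in general and reports exact P values. The ICC is for coverage, and rho, the control percentage, the effect and full response are all assumed. The gain shrinks in the pooled contrasts.

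**Conclusion.** The point holds as one of efficiency. The protocol frames KABP-6C effects as changes, names difference-in-difference for the unlinked analysis, and states no adjustment for a T0 value that is collected and linkable, while it does adjust the primary outcome for baseline.

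For continuous scores and cluster-level percentages the variance saved is (1 - rho)/2: about 35% at rho 0.3, 25% at 0.5 and 5% at 0.9. This rests on randomised municipalities, equal variances at T0 and T1, and large samples. Since the protocol gives no rho, the actual gain cannot be fixed within that range.

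A reader might infer that the KABP-6C results would be biased, or that the trial is underpowered for this objective. The documents support neither. No bias from the stated method is shown, the primary analysis and its sample size are untouched, and no power target exists for KABP-6C.

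**What to change.** In section 11.3.2 (i):
- **Linked respondents:** state that the multilevel models take the T1 score or status as dependent variable, with components and their interactions as planned, and with the individual's T0 value and the municipality T0 mean as covariates.
- **Unlinked analysis:** make T1 adjusted for the municipality T0 mean or percentage the main estimate. Keep the difference-in-difference model as a sensitivity analysis, giving the reason that T0 respondents are volunteers surveyed after allocation.
- **Do not** constrain group means to be equal at T0.
- **Before-after changes:** keep the percentages with change and the medians of differences as description.

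The cost is a few sentences, slightly more model code, and one or two degrees of freedom for the covariates. No new data, linkage or participants are needed.

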Variations in the impact of intervention components will be explored by analyzes stratified by individual characteristics and KAP-6C (at T0). In order to test for significant differences between subgroups, we will examine 95% confidence intervals. In general, we will neither apply predefined statistical significance levels nor correct for multiple testing, but report exact P values. Interaction terms may be included in the models, if indicated.

Models including individual characteristics will be built for an analysis of the determinants of vaccination intentions.

Other analyzes will focus on the change from “intention without vaccination” to “vaccination declaration”; and on the association between individual characteristics, KAP-6C items at T0 or T0-T1 change.

Statistical analyzes will be carried out using STATA software.

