## **(ii) Analysis of secondary objective 2**

A descriptive analysis of the outcomes at their different measurement times is carried out by quantile of social deprivation (FDep) in order to study the existence of a social gradient, which could be the sign of a worsening or of an improvement in social health inequalities with regard to HPV vaccination. The FDep is also introduced as an adjustment variable in the multivariate regression models (see 10.3.1) in order to highlight an association of the level of deprivation with the effectiveness of the intervention, all things being equal. Interactions of the variables of interest with deprivation will also be tested in the models.

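### For the KABP-6C outcomes, subgroup differences are to be tested by examining 95% confidence intervals, which as written does not test the difference; the interaction term that would is left optional

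*Protocol*

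**What the plan says.** Protocol 11.3.2 (i), Analysis of secondary objective 1, covers intention, knowledge, attitudes and practices in adolescents, parents and GPs. It plans multilevel models that allow for cluster randomization, and a difference-in-difference model. On effect modification it says "Variations in the impact of intervention components will be explored by analyzes stratified by individual characteristics and KAP-6C (at T0"). The method for judging whether effects differ follows: "In order to test for significant differences between subgroups, we will examine 95% confidence intervals".

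Two sentences qualify this. One is "In general, we will neither apply predefined statistical significance levels nor correct for multiple testing, but report exact P values". The other is "Interaction terms may be included in the models, if indicated". What would trigger the interaction terms is not stated.

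The protocol is firmer elsewhere. For the primary outcome, 11.3.1 says "Subgroup analyzes will be carried out according to sex, deprivation level (FDep) and considering a modeling approach with interaction terms". For secondary objective 2, 11.3.2 (ii) says "Interactions of the variables of interest with deprivation will also be tested in the models".

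**The concern.** The hypothesis named is that a component's effect is the same in two subgroups, so that the difference of effects is zero. A confidence interval from one stratum speaks only to the effect in that stratum. Setting two such intervals side by side is not a test of the difference, and the reader has to supply the rule. The usual rules err in opposite directions: one is far too strict, the others too lenient.

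The design makes the strict rule stricter. Strata by individual characteristics or by T0 answers lie within the same randomized municipalities, so the stratum estimates share municipality effects. The shared part cancels in the difference but still widens each stratum's interval.

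The paragraph also pulls against itself. It speaks of testing for significance while setting no significance level, and it promises exact P values, yet stratum intervals give no P value for the difference. If the optional interaction term is fitted only after the intervals suggest something, the valid test depends on an invalid screen.

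At stake are the statements about in whom each component changes intention, knowledge or attitudes.

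**Working it through.** **Inputs.** The 95% level comes from 11.3.2 (i). The benchmark is a two-sided 5% test of the difference, which is the level 11.3.1 sets for the primary outcome; objective 1 sets none. Section 11.2 gives 15 municipalities per group and an ICC of 0.05, the latter for vaccination coverage. The protocol gives no subgroup sizes, standard errors, correlations or ICC for KABP-6C outcomes, so those are assumed below. It also states no figure for this comparison, so there is none to reproduce.

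**Notation.** d is the difference between two stratum effects, with standard errors s1 and s2 and correlation ρ. The interaction test at 5% is |d| > 1.96·SE(d), with SE(d) = √(s1² + s2² − 2ρ·s1·s2).

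**1. Non-overlap, independent strata.** The intervals separate when |d| > 1.96(s1 + s2). With r = s2/s1, the threshold in units of SE(d) is c = 1.96(1 + r)/√(1 + r²). Where the interaction test has 80% power, d lies at 1.96 + 0.84 = 2.80 SE(d). Where it has 90%, d lies at 1.96 + 1.28 = 3.24 SE(d). Power of the rule is Φ(2.80 − c) or Φ(3.24 − c).

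| r | c | type I error | power (interaction 80%) | power (interaction 90%) |
|---|---|---|---|---|
| 1 | 2.77 | 0.56% | 51% | 68% |
| 2 | 2.63 | 0.85% | 57% | 73% |
| 3 | 2.48 | 1.3% | 63% | 78% |

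At r = 1, where the interaction test has 50% power, the rule has Φ(1.96 − 2.77) = 21%. It misses more than half of real differences once the interaction test's power is below Φ(2.77 − 1.96), about 79%.

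**2. Non-overlap, shared municipalities.** With equal standard errors, c = 2.77/√(1 − ρ). At an assumed ρ of 0.2, c = 3.10 and power is 38% where the interaction test has 80%. At an assumed ρ of 0.5, c = 3.92 and power is 13%.

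**3. Illustration for this design.** Take 30 municipalities against 30, as in the EMM comparison without vaccination campaign (groups 2 and 4 against 5 and 6). Assume 30 respondents per subgroup per municipality, a proportion of 0.30, a true difference in effects of 10 points, and municipality effects fully or half shared between subgroups.

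- The variance of one stratum effect is 2·(0.30·0.70/30)·[ICC + (1 − ICC)/30].
- At ICC 0.05 this is 0.014 × 0.0817 = 0.00114, so s = 0.0338. Intervals separate only beyond 3.92 × 0.0338 = 0.1325.
- SE(d) is √(0.028 × 0.0317) = 0.0298 (fully shared) or √(0.028 × 0.0567) = 0.0398 (half shared).
- Non-overlap detects Φ((0.10 − 0.1325)/SE(d)) = 14% or 21%. The interaction test detects Φ(0.10/SE(d) − 1.96) = 92% or 71%.
- Non-overlap detects about 42% at ICC 0.02 and about 55% at ICC 0.01. The interaction test stays within 71% to 92% throughout.

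**4. Zero excluded in one stratum but not the other.** With equal true effects, independent strata and power p in each, the probability of a false difference is 2p(1 − p):

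- p = 0.9: 18%
- p = 0.8: 32%
- p = 0.5: 50%
- p = 0.3: 42%

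**5. One estimate outside the other's interval.** With equal standard errors and independent strata, |d| > 1.96·s is |d| > 1.39·SE(d), a type I error of 16.6%.

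**6. Interval for the difference itself.** This matches the interaction test and holds 5%. The text does not say that this is meant.

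**The case against.** The strongest reply is that the sentence fixes no rule. It mentions neither overlap nor exclusion of zero, and examining the 95% interval of the difference would be valid. That reading is possible, but the sentence before it describes stratified analyses, so intervals within strata are the natural meaning. If the interval of the difference was intended, the fix only says so.

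Second, interaction terms are permitted in the same paragraph and multilevel models are already planned. A reader might infer that the protocol rules out the right test. It does not. But an optional term with no stated trigger does not make it the method.

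Third, the analysis is exploratory and disclaims significance levels, so a type I error of 0.56% is measured against a threshold the plan does not adopt. This is fair and limits the weight of the point. It does not rescue a sentence whose stated purpose is to test for significant differences.

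Fourth, 11.3 announces a separate data management and statistical analysis plan, where such detail could sit. That would answer a gap. Here the protocol does state a method, and the wording needs correcting.

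Fifth, the loss under non-overlap depends on unknown quantities. This stands: in the illustration, detection runs from 14% to 55% as the ICC goes from 0.05 to 0.01, and 0.05 was set for coverage.

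**Conclusion.** The point holds: as written, the procedure does not test the hypothesis it names. Under non-overlap with independent strata and equal standard errors, type I error is about 0.56% and power is 51% or 68% where an interaction test has 80% or 90%. Sharing of municipalities lowers that power further. Under discordant significance, false differences arise with probability 2p(1 − p) when effects are equal. These results rest on normal approximations; the protocol supplies no KABP-6C subgroup sizes or correlations with which to say which row applies.

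Two stronger conclusions are tempting and not supported. One is that real subgroup differences will mostly be missed, or that power is near zero. With independent, equal-precision strata, more than half are missed only when the interaction test itself has under about 79% power, and the low figures in the illustration depend on assumed inputs. The other is that the trial's main findings are at risk. They are not: the damage is limited to exploratory subgroup statements on KABP-6C outcomes, since 11.3.1 and 11.3.2 (ii) plan interaction terms.

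**What to change.** In 11.3.2 (i), replace the sentence on examining intervals, and delete the one making interaction terms optional, with text such as:

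*Whether a component's effect differs by a characteristic is estimated and tested through the component × characteristic interaction in the multilevel model with a municipality random effect. The difference in effects is reported with its 95% confidence interval and exact P value. Stratum-specific estimates are descriptive, and their intervals are not compared.*

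In the difference-in-difference model, where the effect is itself a group-by-time interaction, the corresponding term adds the characteristic to that interaction.

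The absence of predefined significance levels and of multiplicity correction can stay, provided the results are presented as exploratory. The cost is a short text change and one extra model term per characteristic. No new data are needed, and the method then agrees with 11.3.1 and 11.3.2 (ii).
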